#### Acceptability

The consultants’ experience in using the structured care model, and the perceived value of this approach, will be explored in qualitative interviews at conclusion of the study. The semistructured interviews will include questions about the value of the additional questions and referral model at eliciting and managing emotional distress and the impact of these additions in building rapport and maintaining a caller-directed approach. The interview will be recorded, partially transcribed, and analyzed according to content analysis facilitated through NVivo qualitative data analysis software (QSR International Pty Ltd. Version 10, 2014). The Consolidated Criteria for Reporting Qualitative Research will be used [39].

#### Costs

The length and number of calls made or received by participants is automatically recorded. Standard hourly rates for consultants will be used to calculate the cost of service delivery. Service provider costs owing to the uptake of referrals in both groups are tracked through the Cancer Council CRM, and standard hourly costs will be applied to provide a full assessment of the cost implications for each of the care models. Standard hourly costs will be derived directly from CIS CRM data.

Participant outcome data and service provider cost data will be submitted to a series of discussion sessions involving consumers and relevant service leads at conclusion of the study. These sessions will explore whether the identified consumer benefits are perceived to be commensurate with the additional service provider costs incurred. The discussion sessions will be guided by the Nominal Group Technique [40]: (1) Service leads will receive a prediscussion report with information such as cost per caller screened under usual and structured care, odds of referral uptake, and average change in distress scores; (2) The roundtable discussion will be led by a group facilitator who will ask for individual feedback recorded in a *round-robin* format; (3) The group will then collectively discuss the feedback until consensus is reached on the cost and benefits of intervention. This discussion will be audio-recorded; and 4) Participants will have the opportunity to provide further comment directly to the research team.

#### Statistical Methods and Sample Size

Descriptive statistics will assess referral uptake rates. Differences between GHQ-28 scores for the structured and usual care groups will be tested using a generalized linear mixed model with fixed effects for the intervention and each time period after baseline. To account for the fact that outcomes are measured at the participant level while randomization is at the consultant level, a normally distributed random intercept for consultants will be included in the model. The parameter of interest from these models will be the estimated coefficient for the intervention term. On the basis of 8 consultants participating, the trial aims to recruit a total of 1512 distressed callers across the 3 steps. The sample size provides the study with approximately 80% power to detect a difference of 0.3 SD in the mean score of the GHQ-28 at an alpha level of .05 and assuming an intracluster correlation of .04. An effect size of .3 was selected based on previous trials of psychoeducation and telephone-administered interventions with patients with cancer [41].

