**Results:**

The structured care model was developed by guideline review and identification of service characteristics to guide mapping decisions; place-card methodology; and clinical vignettes with think-aloud methodology to confirm referral appropriateness. The model includes an additional screening tool (Patient Health Questionnaire-4) and a referral model with 16-20 CIS services. Descriptive statistics will be used to assess referral uptake rates. Differences between GHQ-28 scores for structured and usual care callers will be tested using a generalized linear mixed model with fixed effects for intervention and each time period. The trial will recruit 1512 callers. The sample size will provide the study with approximately 80% power to detect a difference of 0.3 SD in the mean score of the GHQ-28 at an alpha level of .05 and assuming an intra-cluster correlation of .04. A random sample of recorded calls will be reviewed to assess intervention fidelity and contamination. To date, 1835 distressed callers have been invited to participate with 60.71% (1114/1835) enrolled in the study. A total of 692 participants have completed 6-month CATIs. Recruitment is anticipated to end in late 2019.

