### Incorporating and Evaluating Distress Screening Practices in Telephone-Based Services

The International Psycho-Oncology Society emphasized that “Distress should be recognized, monitored, documented and treated promptly at all stages of disease and *in all settings*.” [15]. One setting in which structured care might be implemented routinely is the community-based Australian Cancer Council Cancer Information and Support (CIS) telephone service. The CIS model of care operates in numerous countries [16] including the United Kingdom [17] and Australia [18]. Under the Australian CIS model, health professionals provide emotional, practical, and informational telephone support to both patients and caregivers [18]. Strengths of the model include its ability to assist individuals who are unable to receive traditional face-to-face supportive care owing to geographical isolation or poor physical health [17]. In 2017, the Australian CIS [name] telephone service received 46,000 calls nationally [19], of which, the New South Wales (NSW) CIS received 12,225 calls [20] and Victorian CIS service received 11,429 calls [21].

In total, 2 Australian studies established the acceptability and feasibility of implementing distress screening and tiered care in the CIS context [22,23]. These exploratory studies revealed that, despite screening acceptability, a low proportion of callers take up the referrals that are offered. Poor referral uptake (approximately 20% to 25%) has also been reported in hospital-based services [24,25]. As additional psychosocial care is associated with improved emotional well-being and quality of life, it is critical to maximize the proportion of distressed patients and caregivers acting upon these referrals [26].

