### Aims

To identify the following:

The proportion of distressed people affected by cancer who call the CIS service and take up an offer of referral under the structured care model.Whether the structured care model reduces the level of distress at 6-month follow-up among people affected by cancer when compared with usual care.The relative costs and benefits of structured versus usual care models at 6-month follow-up from the service provider perspective.

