### Hypotheses

At 6-month follow-up:

There will be at least a 20% increase in the proportion of distressed callers who are offered a referral under the structured care model and accept the offer.Distressed callers who receive structured care referrals will report lower scores on the GHQ-28 (0.3 SD lower) at 6 months when compared with those who receive usual care.Structured care will incur higher service delivery costs per distressed caller than usual care. These higher costs will be considered appropriate by the service provider and consumers to reduce caller distress.

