### Study Outcomes

Study outcomes are assessed through 6-month computer assisted telephone interviews (CATIs) with participants; the CIS CRM Systems; and review of audio recordings. The data collection time periods were designed to increase patient recall of referrals in 2 shorter 3-month periods. CATIs are an appropriate method of data collection from participants recruited through a telephone-based support service.

Referral uptake is the primary outcome and is measured as the proportion of participants who report being provided with a referral and report at 6-month follow-up that an action has been taken to progress the referral (ie, an appointment or telephone interaction). Referral uptake was selected as the primary outcome as it can reflect the appropriateness of the type of referral offered to callers under the structured care model. The hypothesized increase of 20% in referral uptake was selected based on internal CIS data in the absence of comparable studies in telephone-based supportive care service uptake. The study-specific questions are tailored to the CIS services; questions were pilot-tested with a consumer advisory panel and reviewed after the first 20 participants.

Distress is measured by the GHQ-28 [31] that is a widely used self-report measure of general psychological distress. The measure uses 28 items to assess perception of health in terms of ability to play a useful part in life; make decisions; overcome difficulties; enjoy normal activities; face problems; and feel confident, worthwhile, and happy [31]. The GHQ-28 has excellent internal consistency, diagnostic accuracy, and test-retest reliability [32,33]. The measure has been used in the Australian community [34] and with patients with cancer [35].

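### Referral uptake is the primary outcome with a comparative hypothesis, but the only analysis stated for it is descriptive; the stepped-wedge model is stated for GHQ-28 alone

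*Protocol article*

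**What the plan says.** Under Study Outcomes the protocol article states: "Referral uptake is the primary outcome and is measured as the proportion of participants who report being provided with a referral" and also report by 6 months that some step was taken on it. The first hypothesis is comparative and directional: "There will be at least a 20% increase in the proportion of distressed callers who are offered a referral under the structured care model"; acceptance of the referral is part of the same condition. Study Outcomes gives the basis of the figure: "The hypothesized increase of 20% in referral uptake was selected based on internal CIS data". No usual-care rate is given there, and nothing says whether the 20% is in percentage points or relative.

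Two places state how uptake will be analysed. The Abstract (Results) says: "Descriptive statistics will be used to assess referral uptake rates". Statistical Methods and Sample Size says: "Descriptive statistics will assess referral uptake rates".

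The sentence after the latter gives GHQ-28 a generalized linear mixed model with fixed effects for intervention and period. A consultant random intercept is added because randomization is by consultant while outcomes are measured on callers. The sample size of 1512 is justified on GHQ-28 only.

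**The concern.** The reason given for the GHQ-28 model applies equally to uptake: the same callers are nested in the same randomized consultants over the same periods. Yet the outcome that carries the primary hypothesis is given a method that yields no effect estimate, interval or test.

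Descriptive rates are also a poor basis for comparison in a stepped wedge. Table 1 has all consultants on usual care in period 1 and all on structured care in period 3, so condition and calendar time are strongly associated. A reader shown two pooled rates could not separate the intervention from any change over time in what callers do. Nor could the reader judge the 20% target, because the two readings of it differ greatly in size.

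**Working it through.** **Inputs from the article.**
- Table 1 and Statistical Methods: 8 consultants, 4 crossing after period 1 and 4 after period 2; 3 periods of 504 callers. That is 504/8 = 63 per consultant-period and 24 cells.
- Statistical Methods: ICC .04, alpha .05 (two-sided assumed), 0.3 SD.
- Results, Progress: 20.8% loss, so 1512 × 0.792 = 1197.5 completers, or 49.9 per cell.

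**Assumptions.**
- The uptake ICC is also .04, and cells are of equal size.
- Usual-care uptake is 20-25%. The article reports this range for another setting: "Poor referral uptake (approximately 20% to 25%) has also been reported in hospital-based services".
- All completers are in the denominator.
- A secular trend, where used, is 2 to 5 points per period.

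**1. The plan's own figure (GHQ-28).** The Hussey-Hughes variance is

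Var = Iσ²(σ² + Tτ²) / [(IU − W)σ² + (U² + ITU − TW − IV)τ²]

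with I = 8, T = 3, U = 12, W = 0 + 16 + 64 = 80, V = 4×4 + 4×1 = 20, τ² = 0.04 and σ² = 0.96/63 = 0.01524.
- Numerator: 8 × 0.01524 × 0.13524 = 0.01649.
- Denominator: 16 × 0.01524 + 32 × 0.04 = 1.5238.
- Variance 0.01082, SE 0.1040 SD.
- Power = Φ(0.3/0.1040 − 1.96) = 82.2%. If 0.3 is in within-consultant SD units, SE is 0.1040/√0.96 = 0.1062 and power is 80.7%.

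The stated figure of about 80% is reproduced, without allowance for loss.

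**2. Confounding of a pooled comparison with period.**
- Usual care: 8 cells in period 1 and 4 in period 2; mean period (8×1 + 4×2)/12 = 1.33.
- Structured care: 4 cells in period 2 and 8 in period 3; mean period (4×2 + 8×3)/12 = 2.67.

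A trend of d points per period shifts the crude difference by 1.33d with no intervention effect: d = 2 gives 2.7 points and d = 5 gives 6.7 points.

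**3. Clustering and the same crude difference.** Each consultant's cell weights (±1/12) sum to ±1/12, so the correct variance in SD units is 8 × (1/144) × ICC + (1 − ICC)/(6m). The variance that ignores clustering is 2/(12m).

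| m per cell | SE ignoring clustering | Correct SE | Ratio | Type I error of a nominal 5% test |
|---|---|---|---|---|
| 63 | 0.0514 | 0.0690 | 75% | 14% |
| 49.9 | 0.0578 | 0.0737 | 78% | 12% |

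Type I error is 2[1 − Φ(1.96 × ratio)], with no trend. At 30% uptake (SD √0.21 = 0.458) the second row is 0.026 against 0.034 on the risk scale.

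**4. Power for the 20% with a period-adjusted, clustered analysis.** At m = 49.9 the step 1 formula gives SE 0.1162 SD. It is multiplied by √[p̄(1 − p̄)], a linear approximation for a binary outcome, where p̄ is the mean of the two rates. Power is Φ(difference/SE − 1.96).

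| Reading | Rates | SE | Power |
|---|---|---|---|
| +20 points | 20% to 40% | 0.0532 | 96.4% |
| +20 points | 25% to 45% | 0.0554 | 95.0% |
| +20% relative | 20% to 24% | 0.0481 | 12.9% |
| +20% relative | 25% to 30% | 0.0519 | 16.0% |

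These use a normal reference. A small-sample correction, or a denominator limited to callers who report a referral, would lower them.

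**The case against.** The article condenses a fuller protocol, and an analysis plan may exist. There are hints of an uptake model. Statistical Methods refers to models in the plural, and the class it names can fit a binary outcome. Costs foresees reporting odds of uptake, and Moderators promises to account for covariates. A reader might infer that the primary hypothesis will never be tested. The documents do not support that; they support only that no test is stated in this article. But none of the hints supplies a model, a period term or a clustering term. The article is also not silent: it states a method for uptake twice and contrasts it with a test for GHQ-28.

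The article does not say that rates will be pooled by condition or given an interval that ignores clustering. Describing uptake by period and sequence would reduce the confounding. This stands, so steps 2 and 3 are conditional. Such a description would still not estimate the hypothesised increase.

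Some stronger readings should be resisted:
- Setting 0.026 against the period-adjusted 0.053 suggests that an unclustered interval is half its proper width. Those SEs belong to different estimators. For the crude difference itself the ratio is about 75-78%, and much of the rest is the price of period adjustment.
- The possible new record system is not evidence of a trend in uptake. Study Design cites it only as a reason to adjust timeframes, and uptake is self-reported by interview.
- Aim 1 speaks only of the proportion who "take up an offer of referral under the structured care model", with no comparator. The Abstract's objective, the Introduction and the first hypothesis are all comparative, so this is editorial.
- Sizing on GHQ-28 is not itself an error. If the 20% is absolute, uptake is the better-powered outcome.

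**Conclusion.** The point holds as a mismatch between the primary comparative hypothesis and the only analysis the article states for it. That mismatch depends on no assumed figure.

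The consequences are conditional. A comparison pooled by condition would carry a bias of 1.33 times the per-period trend; the multiplier follows from Table 1 with equal cells, while the 2 to 5 points are assumed. If clustering were also ignored, the interval would be about a quarter too narrow and type I error about 12-14%, at an assumed ICC of .04.

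The undefined 20% matters separately. Under the assumed base rate, the two readings move power from about 95-96% to 13-16%, so the article does not show whether its primary hypothesis can be answered at this sample size.

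**What to change.** Replace the sentence on descriptive statistics with wording such as:

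> Referral uptake, the primary outcome, will be analysed by the condition allocated to the index-call consultant, using a logistic (or binomial) mixed model with fixed effects for intervention, period and state and a random intercept for consultant, with a small-sample correction for 8 consultants. The odds ratio and the period-adjusted risk difference will be reported with 95% confidence intervals.

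Make the same change in the Abstract. Descriptive rates by period and sequence can be kept alongside.

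State whether the 20% is absolute or relative, give the usual-care rate from the internal data behind it, and report power at the expected number of completers under the chosen denominator.

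The cost is one more model on data already being collected, and a wider interval. At 49.9 completers per cell the period-adjusted SE is 0.1162 SD against 0.0737 for the crude difference with clustering respected, about 1.6 times as wide.

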#### Consultant Randomization

Consultants are randomized to deliver either usual care or structured care during inbound calls with all consultants delivering structured care (ie, PHQ-4 with the referral model) at study completion (Table 1). A randomization table was created by computer software (ie, computerized sequence generation) and using stratified block randomization by state. Owing to the nature of the intervention, consultants are not blinded to the allocation and callers are not informed of consultants’ allocation.

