#### Moderators

Sociodemographic and disease-related characteristics include cancer type, stage of disease, age, gender, postcode, marital status, education, health care card recipient, private health insurance, household income, previous psychological treatment, and/or morbidity and other assistance received since study enrolment. Caller type (patient or caregiver), DT score at inbound CIS call, and reason for contacting the CIS (eg, information, emotional, or practical support) will also be accounted for in study analyses. Subgroup analyses will be conducted for caregivers. Basic information regarding the consultants, such as the number of years at the CIS, will also be incorporated into analyses.

The Health Education Impact Questionnaire (HeiQ) is a 42-item tool for assessing the efficacy and impact of health education and self-management programs for people with chronic diseases [36]. The HeiQ has demonstrated reliability and validity, including with oncology samples, and has been used previously by Cancer Councils to evaluate programs [37,38].

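### The GHQ-28 model that gives the intervention estimate lists no caller covariates, and the promise to account for inbound DT score and caller type does not say whether they enter it

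*Protocol article*

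**What the plan says.** Under Statistical Methods and Sample Size, the protocol article describes the GHQ-28 analysis as a "generalized linear mixed model with fixed effects for the intervention and each time period after baseline". It adds that "a normally distributed random intercept for consultants will be included in the model", and then that "The parameter of interest from these models will be the estimated coefficient for the intervention term". No caller characteristic appears among the model terms.

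The Moderators section lists many sociodemographic and disease variables. It then names "Caller type (patient or caregiver), DT score at inbound CIS call, and reason for contacting the CIS" as things the study analyses will account for. It does not say in which analysis, or whether as main effects or as interactions with the intervention. Caregiver subgroup analyses and consultant characteristics follow in the same paragraph.

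Three other facts bear on the point:

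- Under Consultant Randomization, "consultants are not blinded to the allocation and callers are not informed" of which condition their consultant delivers. Caller Recruitment says that these consultants invite callers at the end of the inbound call.
- The DT is used in both conditions, and a score of 4 or more is an eligibility criterion. The PHQ-4 is part of structured care only, and the abstract places the GHQ-28 in the 3- and 6-month interviews.
- On size: "On the basis of 8 consultants participating, the trial aims to recruit a total of 1512 distressed callers across the 3 steps", giving "approximately 80% power to detect a difference of 0.3 SD in the mean score of the GHQ-28". The calculation is made "at an alpha level of .05 and assuming an intracluster correlation of .04".

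**The concern.** An adjustment covariate enters as a main effect and leaves one intervention coefficient to report. A moderator enters through an interaction, and the coefficient on the intervention term then means something else. The two sections can therefore lead to different headline estimates, and the article does not say which is intended. The Moderators list is long and includes at least one post-enrolment item (other assistance received). If the covariates are not fixed beforehand, the later choice among them is wide.

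The inbound DT is the only baseline distress measure described for both conditions. Without it, the GHQ-28 comparison has no baseline distress value to lean on.

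The design gives a reason to want one. Callers are invited after the call, by someone who knows the condition delivered, and 60.7% of those invited had consented by April 2019 (1114/1835). Who enters the sample can therefore differ by condition. With eight randomized consultants, chance balance of case mix is also weak protection. At stake are some precision and some protection of the estimate against a difference in initial distress or in the patient to caregiver mix.

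**Working it through.** **Inputs from the article.** 8 consultants; 3 periods; 504 callers per period (Table 1), so 504/8 = 63 per consultant-period; four consultants follow the sequence 0-1-1 and four 0-0-1; ICC 0.04; difference 0.3 SD; alpha 0.05. Loss at 6 months is 182/874 = 20.8%.

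**Assumptions.** A two-sided normal test; one consultant effect that is constant over time; a DT to GHQ-28 correlation r of 0.2, 0.3 or 0.4, which the article does not give. The low end is plausible because enrolment truncates DT at 4 or more and the outcome comes six months later. Caller type adds nothing to these figures unless r² is read as the joint share explained by both covariates.

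**Formula.** With I = 8 consultants, T = 3 periods, s² the within-consultant variance divided by the callers per cell, and t² the consultant variance, the standard stepped-wedge variance of the intervention coefficient is

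Var = I·s²·(s² + T·t²) / [(I·U − W)·s² + (U² + I·T·U − T·W − I·V)·t²].

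Here U = 4×2 + 4×1 = 12 is the number of treated cells. W = 0² + 4² + 8² = 80 sums the squared period totals. V = 4×2² + 4×1² = 20 sums the squared consultant totals. So I·U − W = 96 − 80 = 16, and the second bracket is 144 + 288 − 240 − 160 = 32.

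**The plan's own figure.** With total variance 1, s² = 0.96/63 = 0.01524 and t² = 0.04:

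- Var = 8 × 0.01524 × (0.01524 + 0.12) / (16 × 0.01524 + 32 × 0.04) = 0.01649/1.5238 = 0.01082, so SE = 0.104.
- Power = Φ(0.3/0.104 − 1.96) = 82.2%.
- If 0.3 SD refers to the within-consultant SD, SE = 0.104/√0.96 = 0.106 and power is 80.7%.

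The stated figure of about 80% is thus reproduced without any covariate.

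**With adjustment.** Multiply the within-consultant variance by 1 − r² and leave the consultant variance unchanged. At 20.8% loss, 1512 × 692/874 is about 1197 scores, or 49.9 per cell. Total-SD reading:

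| | no covariate | r = 0.2 | r = 0.3 | r = 0.4 |
|---|---|---|---|---|
| SE, 1512 | 0.104 | 0.102 | 0.099 | 0.096 |
| Power, 1512 | 82.2% | 83.7% | 85.5% | 88.0% |
| SE, 1197 | 0.116 | 0.114 | 0.111 | 0.107 |
| Power, 1197 | 73.3% | 74.9% | 77.0% | 80.1% |

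On the within-SD reading, the power rows become 80.7%, 82.2%, 84.0%, 86.7% and 71.6%, 73.2%, 75.3%, 78.5%. Returning to 80% after the loss needs r² of about 0.16 (total SD) to 0.195 (within SD).

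**Shift from imbalance.** The shift in the unadjusted estimate is about r × the DT difference in SD units, where the difference is what remains after period and consultant effects. Residual differences of 0.1 to 0.3 SD are assumed. The smallest case is 0.2 × 0.1 = 0.02 SD (0.02/0.3 = 7% of the target difference). The largest is 0.4 × 0.3 = 0.12 SD (40% of the target).

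**The case against.** The strongest reply is that nothing is excluded. The statistical section gives the stepped-wedge skeleton and never says that these are the only terms. It speaks of models in the plural, and the Moderators section uses the language of adjustment. The two can be read together, and the exact covariate set is commonly left to an analysis plan, which is not shown here. This much stands: a reader might infer that the headline estimate will be unadjusted and that power and case-mix protection have been abandoned, but the article does not say so. What remains is that the article makes both statements and leaves their connection open for the one coefficient that it singles out.

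A reader might also infer that the power statement is wrong. It is not: about 80% is reached with no covariates. The shortfall at about 1197 scores comes from loss to follow-up, not from the missing covariates.

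A third tempting argument is that structured-care callers come later in calendar time. The period effects already handle trends common to all consultants, so only differences tied to condition or consultant remain. Caller Recruitment also plans an analysis of decliners for consent bias; that can reveal selection but does not adjust the estimate for it.

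Two smaller points stand. The DT is taken by an unblinded consultant, so it is not a perfectly clean baseline. Its completeness is inferred from the eligibility rule rather than stated.

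**Conclusion.** The point holds as a gap between two sections: adjustment of the GHQ-28 intervention coefficient for inbound DT score and caller type is promised loosely but not secured in the model. No stated figure is wrong because of it.

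The benefit of securing it is real but modest: on the total-SD reading, about 1.5 to 6 points of power with 1512 callers and about 1.6 to 7 points at 20.8% loss. The possible shift of 0.02 to 0.12 SD is a range of scenarios, not an estimate, since neither the correlation nor the imbalance is in the article; its upper end needs both assumptions at their highest.

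The weight is limited because the article names referral uptake, not GHQ-28, as the primary outcome. It is not negligible, because GHQ-28 drives the sample size and is the only outcome for which a model is given. The change is worth making, but the analysis is not invalid without it.

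**What to change.** - In Statistical Methods and Sample Size, list inbound DT score and caller type (patient or caregiver) as prespecified fixed effects, beside intervention, period and the consultant random intercept. State that the intervention coefficient from this model is the parameter of interest.
- Report the model without the two covariates as a sensitivity analysis.
- In Moderators, separate adjustment covariates from variables examined as effect modifiers, and say which role reason for contact has.

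The cost is a sentence or two and no new data. DT score decides eligibility, so every enrolled caller should have one. Caller type was accounted for in all participants at the April 2019 count (624 + 490 = 1114). The choice should be fixed before the outcome data are analysed; at that report, recruitment and follow-up were still under way.

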## Methods

### Study Design

The stepped-wedge trial is conducted with the Cancer Council NSW and Victoria CIS [name] line. The structured care model is sequentially rolled out with CIS consultants randomly allocated to transition to structured care over 3 intervention periods (Table 1). There is a 1-month transition period between each intervention period. Transition periods are included in reporting guidelines for stepped-wedge trials [27]; the transition periods allow for consultants to trial the new structured care call content (PHQ-4 and referral model), discuss and iteratively refine new content with other structured care consultants and receive feedback from the research team.

On the basis of previous CIS call volumes, the trial is approximately 24 months with the opportunity to adjust timeframes in accordance with CIS caller recruitment rates and other internal requirements (eg, implementation of a new electronic medical record system). The study is reported according to SPIRIT recommendations [28].

**Table 1 table1:** Consultant allocation to intervention periods with caller sample size.

Consultant^a^	Intervention period (n=504)				
	1	Transition	2	Transition	3
A	Usual care	→	Structured care	—^b^	Structured care
B	Usual care	→	Structured care	—^b^	Structured care
C	Usual care	→	Structured care	—^b^	Structured care
D	Usual care	→	Structured care	—^b^	Structured care
E	Usual care	—^b^	Usual care	→	Structured care
F	Usual care	—^b^	Usual care	→	Structured care
G	Usual care	—^b^	Usual care	→	Structured care
H	Usual care	—^b^	Usual care	→	Structured care

^a^Each Cancer Information and Support (CIS) service has at least 4 consultants participating in the study.

^b^Not applicable. No transition required.

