## Results

### Progress

As of April 2019, 1835 eligible CIS callers have been invited to participate in the study by CIS consultants. A total of 1114 (60.70%, 1114/1835) individuals consented to participate; 372 (20.27%, 372/1835) declined to participate; and 180 (9.81%, 180/1835) did not respond to the invitation to participate after postal and telephone reminders. The consent status of the remaining 79 individuals is not yet known, and the individuals are currently receiving follow-up reminders through phone and email prompts.

Of the 1114 consenting participants, 692 have now completed the 6-month CATI. From the start of the study, 182 enrolled participants did not complete their 6-month CATI—this represents a lost-to-follow-up of 20.8% (182/874). Just over half of the current sample (56.01%, 624/1114) are patients. The remaining 44.00% (490/1114) of participants are individuals supporting someone with a cancer diagnosis, in remission or bereaved.

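### The 80% power for 6-month GHQ-28 is attached to 1512 recruits; at the article's interim 20.8% loss to follow-up it is about 73%

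*Protocol article*

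**What the plan says.** In the protocol article, Statistical Methods and Sample Size gives the target as "On the basis of 8 consultants participating, the trial aims to recruit a total of 1512 distressed callers across the 3 steps". The next sentence attaches the power to that number: "The sample size provides the study with approximately 80% power to detect a difference of 0.3 SD in the mean score of the GHQ-28". Its other inputs are a significance level of .05 and an ICC of 0.04. The abstract likewise presents 1512 as the number to be recruited.

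Table 1 (Study Design) gives 504 callers per intervention period, and 3 × 504 = 1512. All eight consultants give usual care in period 1, four change to structured care before period 2, and the other four before period 3. The analysis model has fixed effects for intervention and period and a random intercept for consultant.

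The second hypothesis places the GHQ-28 comparison at 6 months. The Progress section reports, as of April 2019, 692 completed 6-month interviews and 182 participants who did not complete theirs: "this represents a lost-to-follow-up of 20.8% (182/874". The article does not connect this loss with the power statement.

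**The concern.** A caller without a 6-month interview supplies no 6-month GHQ-28 score. If the calculation behind the stated power used 1512 as the number analysed, then calling 1512 the number recruited leaves no room for loss. The article's own loss is about one in five.

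Referral uptake is the named primary outcome, but the GHQ-28 difference is the only comparison for which the article states power. The distress results will also be set beside service costs in the planned discussions with service leads and consumers. A GHQ-28 result that showed no difference would be read against a sensitivity the trial is not expected to have.

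**Working it through.** **Inputs from the article**

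- 8 consultants, 3 periods, 1512 callers: 1512 / 24 = 63 per consultant and period.
- Allocation as in Table 1.
- ICC 0.04, alpha .05, difference 0.3 SD.
- Loss: 182 / (692 + 182) = 182 / 874 = 20.8%.

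**Assumptions, because the article does not state them**

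- Two-sided test with a normal reference.
- 0.3 in units of total SD. The alternative, within-consultant SD, is shown alongside.
- Loss spread evenly over consultants and periods.
- No covariates beyond intervention and period, as in the stated model.

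**Formula**

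The model described is the standard stepped-wedge model with a random cluster intercept (Hussey-Hughes). With total variance 1, τ² = 0.04 and σ² = 0.96 / m, where m is the number analysed per consultant and period:

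Var = I σ² (σ² + T τ²) / [(I U − W) σ² + (U² + I T U − T W − I V) τ²]

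Table 1 gives:

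- I = 8 and T = 3
- U = 4×2 + 4×1 = 12
- W = 0² + 4² + 8² = 80
- V = 4×2² + 4×1² = 20
- I U − W = 96 − 80 = 16
- U² + I T U − T W − I V = 144 + 288 − 240 − 160 = 32

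Power = Φ(0.3 / SE − 1.96). If 0.3 is in within-consultant SD, 0.3 becomes 0.3 × √0.96 = 0.294.

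**Step 1: reproduce the stated power, all 1512 analysed (m = 63)**

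σ² = 0.96 / 63 = 0.01524

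Var = 8 × 0.01524 × (0.01524 + 0.12) / (16 × 0.01524 + 32 × 0.04) = 0.01649 / 1.52381 = 0.01082, so SE = 0.1040

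Power = Φ(2.884 − 1.96) = 82.2%, or 80.7% in within-consultant SD. This agrees with the stated value of approximately 80%, with every recruit counted as analysed.

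**Step 2: apply the reported loss**

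1512 × (1 − 182/874) = 1197, so m = 49.9 and σ² = 0.01925

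Var = 8 × 0.01925 × (0.01925 + 0.12) / (16 × 0.01925 + 1.28) = 0.02144 / 1.58793 = 0.01350, so SE = 0.1162

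Power = Φ(2.582 − 1.96) = 73.3%, or 71.6% in within-consultant SD.

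Difference detectable with 80% power: (1.960 + 0.842) × 0.1162 = 0.33 SD, against 2.802 × 0.1040 = 0.29 SD with no loss.

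**Step 3: how much loss the stated power can absorb**

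Power reaches 80% at about 1423 analysed: 1 − 1423/1512 = 5.9% loss. In within-consultant SD it takes about 1485: 1 − 1485/1512 = 1.8% loss.

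**Step 4: other loss rates (total SD)**

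| Loss | Analysed | SE | Power |
|---|---|---|---|
| 0% | 1512 | 0.1040 | 82.2% |
| 10% | 1361 | 0.1094 | 78.3% |
| 15% | 1285 | 0.1124 | 76.1% |
| 20.8% | 1197 | 0.1162 | 73.3% |
| 25% | 1134 | 0.1192 | 71.1% |

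**Step 5: sensitivity to the ICC**

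At an ICC of 0.01, 0.04 and 0.10, power with 1197 analysed is 76.8%, 73.3% and 74.4%, against 84.9%, 82.2% and 83.4% with 1512. The gap does not depend on the ICC chosen.

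**The case against.** The strongest reply is that the article condenses a fuller protocol that may contain an allowance for loss. If Table 1's 504 per period counted completers, the power claim would stand. But the article states a number recruited and a power together, and both the abstract and the sample-size section call 1512 the number recruited. An allowance elsewhere would make that pairing wrong rather than rescue it.

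Three further points have some force:

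- **Sidedness.** It is not stated, and the second hypothesis is directional. A one-sided .05 test with 1197 analysed would have 82.6% power (81.2% in within-consultant SD). Nothing in the article says the test is one-sided.
- **Covariates.** The Moderators section says caller type, Distress Thermometer score and reason for contact will be taken into account. If covariates explained about 16% of the within-consultant variance, 1197 completers would give about 80% power. That percentage is an assumption, and neither the stated model nor the power statement includes these covariates. The 73% should therefore be labelled as unadjusted.
- **The loss rate.** The 20.8% is an interim figure from April 2019, with recruitment still open, and need not be the final rate. Hence the range in the working.

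A reader might also infer more than the article supports:

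- **That 80% power needs every one of the 1512 recruits.** It does not; about 1423 with a score are enough.
- **That power can be worked out from how the periods actually filled.** The article gives the total of 1114 enrolled by April 2019 but not the split by period. With 398 left for period 3 and 20.8% loss, assumed splits of 714/400 and 400/714 give about 67% and 80%, so the assumption decides the answer.

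**Conclusion.** The point holds as a mismatch between the number the power is attached to and the number that would be analysed. The stated figure reproduces from its inputs, so the sample-size calculation itself is not at fault. It is reached only with at most about 6% loss (2% in within-consultant SD), and the article reports 20.8%. At that rate power is about 73% (72%), a shortfall of about 7 to 8 points against 80%, and about 9 points against the same calculation with no loss.

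The result rests on a two-sided .05 test, an unadjusted model, even loss across consultants and periods, and an interim loss rate.

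This should be fixed, but it is not critical. The shortfall is moderate, the outcome is not the primary one, and the remedy is wording. A reader might infer that the design fails or that more callers must be enrolled; the article does not support that, because 1197 completers still give 80% power for a difference only slightly larger than the one planned.

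**What to change.** In Statistical Methods and Sample Size, and in the abstract, state power on the number expected to have a 6-month score. For example: 1512 recruited; at the 20.8% loss observed to April 2019, about 1197 with a 6-month GHQ-28, giving about 73% power for 0.3 SD, or 80% power for about 0.33 SD. Mark the loss rate as an interim observation rather than a planning assumption.

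In the same place, say that 504 per period counts recruits, whether the test is one- or two-sided, and whether 0.3 is in total or within-consultant SD.

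The cost is a few words and a less favourable power figure. Enrolment, analysis and trial conduct do not change.
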